### RCT analyses

#### Sample size

Sample size is calculated using the model of Twisk [56]. This model is suitable for multiple measurements over time, but can also be used for cluster randomization. With the ratio of the number of subjects in the compared groups being 1 (*r*), a correlation coefficient of the repeated measurements of 0.20 (ρ), a conservative difference between the groups in the mean value of social functioning of 0.25 (*v*), and a power of 1-β = 0.80, the number of participants needed is 151 for each condition at T2 measurement (α = 0.05, two-tailed). Taking into account an attrition rate of 15% for loss due to follow-up or consent withdrawal, 173 participants per condition need to be recruited to achieve the required power.$$ N=\frac{Z\left(1-\alpha /2\right)+Z\left(1-\beta \right)\ 2\ \sigma 2\left(r+1\right)\left[1+\left(T-1\right)\rho \right]}{v2r\ T} $$

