#### Statistical analyses

Data will be analyzed according to the ‘intention to treat’ principle, meaning that F-ACT teams (and thus clients) that are assigned to either experimental or control condition in randomization, will be analyzed accordingly. Because of the cluster design and multiple measurements over time, generalized linear mixed models (GLMM) will be used with SPSS (version 22); depending on the distribution of the outcome variable a logistic regression model or a linear regression model will be adopted. GLMM is robust with respect to missing data [57], which is not uncommon in research among outpatients with SMI. Therefore, multiple imputation is not necessary. To analyze the effect of the Victoria intervention on the main outcomes, differences in societal participation and victimization, both conditions will be compared after 9 and 18 months follow-up with time as a categorical variable. Measurements over time are nested within participants; therefore, random slopes will be added for time. Random intercepts will be added for the participants. The same procedure will be adopted for secondary outcome measures. Furthermore, possible confounders will be examined, such as socio-demographic characteristics, current diagnosis, number of years in MHC, or perpetration on whether they need to be added to the model. Only significant confounders will be added to the final model. In all analyses performed, two-tailed *p*-values < 0.05 are considered significant. Finally, Akaike’s Information Criterion (AIC) will be used for the selection of the final model that fits the data best and is the most generalizable [58].

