A final strength of the study is the multi-method approach. A process evaluation will be conducted to examine the implementation process of the intervention. Studies with a similar target population that examine complex interventions in a RCT often find no treatment effect, due to, for example, implementation or fidelity issues [62]. Within the design of an RCT, normally, there is little room for examining the implementation process, leading to a black box in explaining the results. Therefore, the UK Medical Research Council advises conducting a process evaluation, to understand context mechanisms and provide insights on implementation and fidelity [63]. For this reason, we do include a process evaluation and a longitudinal follow-up on effects, using a cluster RCT.

One of the main challenges in this study lies in the fact that the Victoria intervention is a complex intervention, encompassing characteristics of the local context, and the complexity of causal relations between intervention and outcomes [36]. MHPs in the participating teams sometimes work in multiple teams or, due to reorganization, they shift from one team to the other. This brings challenges in the implementation of the intervention. To address this, a strong collaboration is created between the two MHC institutions and the university in this project, with shared goals and input. Additionally, the process evaluation will be helpful in following the implementation process.

Another challenge of this study, and of most other studies among outpatients with SMI and follow-up measurements, is the dropout risk in the cluster RCT. In the sample size calculation, we take this into account by estimating a 15% loss to follow-up, and using effect sizes that may be considered conservative, compared to effect sizes found in other studies [64]. This leads to 347 required respondents at baseline measurement. Moreover, with the help of the MHPs, a contact plan, and by giving clients incentives for participating, we aim to prevent dropout as much as possible.

Finally, due to novelty of the Victoria intervention, there is no valid fidelity measure. Therefore, in this project a new fidelity checklist will be developed and used. To increase validity in measuring fidelity, we use triangulation by also including qualitative analyses of the recordings of the supervision meetings and questionnaires for both clients and MHP, as explained in the methods section.

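### Minor arithmetic error: the 15% attrition allowance multiplies by 1.15 instead of dividing by 0.85, so 173 recruits per condition leave about 147 at T2, not the required 151

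*Protocol article*

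**What the plan says.** In the protocol article, the section on sample size uses a repeated-measures formula with these inputs: "α = 0.05, two-tailed"; "a power of 1-β = 0.80"; an allocation ratio of 1; "a correlation coefficient of the repeated measurements of 0.20"; and "a conservative difference between the groups in the mean value of social functioning of 0.25". The result is 151 per condition, described as the number needed at the T2 measurement. The allowance for loss follows: "Taking into account an attrition rate of 15% for loss due to follow-up or consent withdrawal, 173 participants per condition need to be recruited". The sentence ends by saying that this number achieves the required power.

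The Discussion returns to dropout as a challenge of the study, repeats the 15% loss to follow-up, and concludes: "This leads to 347 required respondents at baseline measurement".

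The inflation formula itself is not written out in either place.

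**The concern.** An attrition rate is a proportion of the people who enter the study. To keep 151 after losing 15%, the number recruited must satisfy N × 0.85 ≥ 151. Adding 15% of 151 to 151 answers a different question and always gives too few. The printed targets look like the second calculation, with the fraction then dropped rather than rounded up.

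If so, the statement that 173 per condition achieves the required power fails under the same paragraph's own assumptions. There is almost no slack to absorb the error, because the 151 is itself 150.7 rounded up. The Discussion also names sufficient power as a major strength and says that the calculation takes dropout into account, so the figure should be right as printed.

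**Working it through.** **Inputs from the sample size section.** α = 0.05 two-sided, power 0.80, r = 1, ρ = 0.20, v = 0.25, required n at T2 = 151 per condition, attrition 15%, target 173 per condition. From the Discussion: target 347 in total.

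**Assumptions.** The values of T and σ are not given. T = 2 follows from the analysis section ("both conditions will be compared after 9 and 18 months follow-up with time as a categorical variable"), and σ = 1 treats 0.25 as a standardised difference. They are needed only for the power figures; the attrition check does not use them.

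**1. Reproduce the 151.** The formula, with the sum of the two normal quantiles squared, is

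N = (z₁₋α/₂ + z₁₋β)² σ² (r + 1)[1 + (T − 1)ρ] / (v² r T)

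= 7.849 × 2 × 1.20 / (0.0625 × 2) = 150.70, rounded up to 151.

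T = 1 would give 251.2 and T = 3 would give 117.2, so T = 2 with σ = 1 is the reading that matches.

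**2. Reproduce the targets.**

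| Rule | Per condition (from 151) | Total (from 302) |
|---|---|---|
| × 1.15 | 173.65 | 347.3 |
| ÷ 0.85 | 177.65 | 355.3 |
| Printed | 173 | 347 |

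Both printed figures are the × 1.15 results rounded down. Neither agrees with division by 0.85, which gives 178 per condition and 356 in total.

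**3. What the printed targets leave at 15% loss.** 173 × 0.85 = 147.05 per condition, about 4 short of 151. 347 × 0.85 = 294.95 in total, about 7 short of 302. For comparison, 178 × 0.85 = 151.3.

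**4. Attrition that the printed targets tolerate.** 1 − 151/173 = 12.7% per condition; 1 − 302/347 = 13.0% in total.

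**5. Power by the protocol's formula.** With T = 2 and σ = 1 the variance of the difference is 1.2/n, so power = Φ(0.25 / √(1.2/n) − 1.96).

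- n = 151: Φ(2.804 − 1.96) = 80.1%
- n = 147: Φ(2.767 − 1.96) = 79.0%

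**6. Power when some lost participants were seen at 9 months.** Of 173 recruits, 147 complete and 26 are lost. With the same structure (ρ = 0.20, σ = 1, one effect common to both follow-ups) and the lost participants' 9-month data included:

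| Lost participants per condition with 9-month data | Power |
|---|---|
| 0 of 26 | 79.0% |
| 7 of 26 | 80.1% |
| 13 of 26 | 81.0% |
| 26 of 26 | 82.9% |

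The protocol article does not say when losses are expected, so this is a range and not an estimate.

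**The case against.** The arithmetic is hard to dispute; the case on the other side is about consequence, and most of it stands.

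- **The power loss may be nil.** The planned mixed model uses whatever follow-up data a participant gave. If about a quarter of those lost (7 of 26) had a 9-month interview, power is back at 80.1%. This stands, and it makes 79% a lower bound. It does not rescue the printed target, because the sample size section sets 151 as the number needed at T2 and inflates for exactly that.
- **The shortfall lies within the imprecision of the inputs.** The corrected 178 is 2.9% above 173. Changing ρ from 0.20 to 0.17, or v from 0.25 to 0.253, would bring the requirement down to about 147. This also stands, as a reason to call the error minor.
- **No described procedure depends on the figure.** A reader might infer that teams will stop recruiting at 173. The section on clients says that all clients of the participating teams will be asked, the teams' caseload is over 1500, and nothing in the article makes 173 or 347 a stopping point. The inference is not supported. Equally, the caseload does not show that 178 will be reached, since no eligibility or consent rate is given.
- **346 against 347 is not a conflict of plans.** Twice 173 is 346, but the difference of one comes from rounding down the same calculation at two levels. It needs tidying and carries no weight of its own.

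The condensed format of an article excuses omissions, but not a printed figure that fails its own paragraph.

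**Conclusion.** The recruitment target is wrong as stated, and the error is minor. At the protocol's own 15% attrition, 173 per condition leave about 147 at T2, where 151 are required. The correct figure is 178 per condition (356 in total), which is 5 more per condition and 9 more than the printed total. This rests only on the printed 151, 15%, 173 and 347.

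The effect on power is at most about 1.1 percentage points (80.1% to 79.0%). It may be nothing, depending on how many of those lost give 9-month data. These power figures assume T = 2, σ = 1 and the protocol's formula.

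A reader might conclude that the trial is underpowered because of this slip, or that its expected power is 79%. The article supports neither. Whether the formula deals adequately with clustering is a separate question and adds nothing to the size of this error.

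**What to change.** Give one consistent figure in the sample size section and the Discussion. Either:

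1. restate the requirement as 178 per condition and 356 in total (151 / 0.85, rounded up); or
2. keep 173 per condition, state the total as 346, and add that this yields 151 at T2 only if attrition is at most 12.7%. Add also that at 15% attrition the protocol's formula gives about 79% power as a lower bound (lost participants contribute no follow-up data), and more if they contribute 9-month data to the mixed model.

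The second option costs only a text correction in two places. The first also raises the stated requirement by 5 per condition. It changes no described procedure, since all clients of the teams are invited anyway, but the article gives no eligibility or consent rate from which to judge whether the higher number is attainable. The analysis does not change under either option.

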#### Statistical analyses

Data will be analyzed according to the ‘intention to treat’ principle, meaning that F-ACT teams (and thus clients) that are assigned to either experimental or control condition in randomization, will be analyzed accordingly. Because of the cluster design and multiple measurements over time, generalized linear mixed models (GLMM) will be used with SPSS (version 22); depending on the distribution of the outcome variable a logistic regression model or a linear regression model will be adopted. GLMM is robust with respect to missing data [57], which is not uncommon in research among outpatients with SMI. Therefore, multiple imputation is not necessary. To analyze the effect of the Victoria intervention on the main outcomes, differences in societal participation and victimization, both conditions will be compared after 9 and 18 months follow-up with time as a categorical variable. Measurements over time are nested within participants; therefore, random slopes will be added for time. Random intercepts will be added for the participants. The same procedure will be adopted for secondary outcome measures. Furthermore, possible confounders will be examined, such as socio-demographic characteristics, current diagnosis, number of years in MHC, or perpetration on whether they need to be added to the model. Only significant confounders will be added to the final model. In all analyses performed, two-tailed *p*-values < 0.05 are considered significant. Finally, Akaike’s Information Criterion (AIC) will be used for the selection of the final model that fits the data best and is the most generalizable [58].

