## Methods

### Design

This study includes: 1) a process evaluation and 2) a two-armed multi center cluster randomized controlled trial (RCT) to follow the implementation process and determine the effectiveness of the Victoria intervention. Participants include adult clients of eight F-ACT teams who are interviewed about their victimization experiences and rehabilitation process at three points in time: at baseline, and after 9 and 18 months. Study characteristics are described according to SPIRIT guidelines [37]. This study was approved by the Medical Ethical Committee of the Elisabeth Hospital in Tilburg (NL53845.028.15) on the 18th of November 2015 for all participating sites. The study is registered with the Dutch Trial Register (NTR 5585).

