#### Randomization and blinding

The participating teams will be randomly allocated to either the experimental or control condition by an independent senior researcher at Tilburg University, stratified by mental health organization. Cluster randomization was chosen as individual randomization would mean reassigning clients from their regular case managers and was therefore considered to be ethically undesirable. Moreover, cluster randomization reduces risks of contamination between the intervention and control group, as the intervention method is team based. We will monitor staff changes as well as clients switching teams to correct for in statistical analyses.

Due to the nature of the intervention, both the MHP and researchers cannot be unaware of the allocation to the conditions, but they are strongly advised not to disclose to the participating clients whether they receive care from an experimental or control team.

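### The stated mixed model has random effects for participants and time but none for team, the unit of randomisation, so follow-up comparisons between arms are anti-conservative unless team effects are negligible

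*Protocol article*

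**What the plan says.** The Randomization and blinding section makes the team the unit of allocation: "The participating teams will be randomly allocated to either the experimental or control condition", stratified by mental health organisation. The Design section gives the number of clusters: "Participants include adult clients of eight F-ACT teams".

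The Statistical analyses section starts from that design: "Because of the cluster design and multiple measurements over time, generalized linear mixed models (GLMM) will be used". It then sets out the random part in two sentences: "Measurements over time are nested within participants; therefore, random slopes will be added for time", followed by "Random intercepts will be added for the participants". The comparison of interest is described as "both conditions will be compared after 9 and 18 months follow-up with time as a categorical variable", and the threshold is that "two-tailed *p*-values < 0.05 are considered significant". The same procedure is extended to the secondary outcomes, and the AIC is used to choose the final model.

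The article names no random or fixed effect for team, no cluster-robust variance and no team-level analysis. The only correlation in the Sample size section is 0.20, for the repeated measurements.

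**The concern.** In a cluster-randomised trial the arm effect has to be judged against the variation between clusters. A random intercept for participants describes the correlation between one person's three interviews. It says nothing about two clients of the same team being more alike than two clients of different teams. As written, the model treats about 300 clients as if each had been allocated separately, and tests arm on hundreds of degrees of freedom when eight teams in two arms provide about six.

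If outcomes vary between teams at all, the standard error of a between-arm difference at follow-up is then too small. A nominally significant result on social functioning or victimisation could come from four teams happening to differ from four others. The AIC gives no protection, because no team term is among the candidates described.

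**Working it through.** **Inputs from the article.** 8 teams; 151 participants per condition at T2; correlation of repeated measurements ρ = 0.20; difference v = 0.25; two-sided α = 0.05; power 0.80; allocation ratio r = 1.

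**Assumptions, not in the article.** Four teams per arm; equal team sizes, so m = 151/4 = 37.75; SD σ = 1; team ICC from 0.01 to 0.05.

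**Step 1: reproduce the sample size.** N = (z₁₋α/₂ + z₁₋β)² σ² (r+1)[1+(T−1)ρ] / (v² r T). With T = 2 follow-ups: (1.960 + 0.842)² × 2 × 1.2 / (0.0625 × 2) = 150.7, so 151, as stated. T = 3 gives 118 and T = 1 gives 252. The stated figure therefore uses the within-person correlation only, and no allowance for teams enters it.

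**Step 2: difference at one follow-up.** Design effect DE = 1 + (m−1) × ICC. The true SE is √DE times the model SE, so type I error = 2 × [1 − Φ(1.96/√DE)].

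| ICC | DE | √DE | Type I error |
|---|---|---|---|
| 0 | 1.00 | 1.00 | 5.0% |
| 0.005 | 1.18 | 1.09 | 7.2% |
| 0.01 | 1.37 | 1.17 | 9.4% |
| 0.02 | 1.74 | 1.32 | 13.7% |
| 0.05 | 2.84 | 1.68 | 24.5% |

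**Step 3: average of both follow-ups.** The variance of a person's mean is (1+ρ)/2 = 0.6. With a team effect constant over time, the effective ICC is ICC/0.6. DE = 1.61, 2.23 and 4.06 at ICC 0.01, 0.02 and 0.05, so type I error = 12.3%, 18.9% and 33.1%.

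**Step 4: change from baseline (condition-by-time contrast).** The variance of a person's change is 2(1−ρ) = 1.6. If team effects at two visits correlate c, the between-team variance of change is 2 × ICC × (1−c), so DE = 1 + (m−1) × 2 × ICC × (1−c)/1.6.

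| ICC | c = 1 | c = 0.8 | c = 0.5 |
|---|---|---|---|
| 0.01 | 5.0% | 6.1% | 7.7% |
| 0.02 | 5.0% | 7.2% | 10.5% |
| 0.05 | 5.0% | 10.5% | 18.1% |

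**Step 5: simulation check.** 3,000 replicates, 8 teams of 38, constant team effect. Participant-level tests rejected in 9.1%, 13.3% and 25.7% of runs for the T2 difference, and in 11.9%, 18.7% and 34.8% for the average, at ICC 0.01, 0.02 and 0.05. A team-level t-test on 6 df rejected in 4.4% to 5.4% across all settings run. With balanced data, participant-level t-tests and covariate-adjusted comparisons stood in for the participant-only model; the full mixed model was not fitted.

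**Step 6: power once teams are respected.** Team-level test on the average of both follow-ups, 6 df, difference 0.25, 151 per arm: about 65% at ICC 0, and 46%, 35% and 22% at ICC 0.01, 0.02 and 0.05.

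**Step 7: the random time effects.** Three visits give a 3×3 within-person covariance with 6 parameters. A random intercept plus two categorical time effects with free covariances uses 6, and the residual makes 7, which is not identified. A linear random slope with free covariance uses 4 (two variances, one covariance, one residual), as does a diagonal structure for the two time dummies with intercept and residual. Both of these are identified.

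**The case against.** The best defence is that the section mentions the cluster design and that a journal article condenses a fuller plan, so a team level may be implied. That would carry weight if the random structure had been left unstated. It is stated, and the reason given for it is nesting within participants. The promise in Randomization and blinding to correct for staff changes and clients switching teams concerns movement between teams and is not a team effect.

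A second objection concerns size, and it largely stands. A reader might infer that type I error is well above 5% as a matter of fact. The documents do not support that, because they give no ICC for any outcome. If the ICC is near zero, or if arm is tested as change from baseline with fully stable team effects, the error stays near 5%. Nor is 12% to 33% the natural headline: comparing conditions after 9 and 18 months with categorical time points to visit-specific differences, for which the range is 9% to 25%. Full stability is nonetheless a strong assumption here, since training and supervision are delivered to teams and the Discussion describes reorganisation and staff moving between teams.

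A reader might also infer that standard errors are too small for every outcome. That is not shown: the ICC is unknown for each one, and knowledge on rehabilitation is measured on professionals rather than clients.

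Finally, a reader might conclude that the random slopes cannot be estimated. The article attaches categorical time to the comparison of conditions and states no covariance structure for the random part. Non-identifiability follows under one reading and not under others, so this is an ambiguity to clear up.

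**Conclusion.** The point holds in conditional form. The model as written leaves out the unit of randomisation and gives anti-conservative inference whenever outcomes vary between teams in the contrast tested. This is a fault in what is stated, not a detail left to another document. Its size rests on an assumed ICC of 0.01 to 0.05 and four equal teams per arm: about 9% to 25% type I error at one follow-up, 12% to 33% for the average of both, and 5% to 18% for change from baseline depending on the stability of team effects. It should be corrected before analysis, because a nominally significant arm effect from this model could not be taken at face value. The covariance structure of the time effects is a secondary matter of clarification.

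**What to change.** In the Statistical analyses section:

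- Add a random intercept for team and a random team-by-time term, or specify a team-level analysis of follow-up or change. A team intercept alone is not enough, because it cancels from a change-from-baseline contrast.
- Include organisation, the randomisation stratum, in the model.
- Test arm with small-sample degrees of freedom suited to eight teams, for example Satterthwaite or Kenward-Roger: about 6, or 5 with the stratum. A team-level t-test can serve as a check.
- Keep the team terms whatever their estimates or the AIC.
- State the covariance structure of the random time effects and choose one that is identified with three visits.

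The edit itself is a matter of wording. The cost lies in precision: confidence intervals widen, and the design value of "a power of 1-β = 0.80" no longer describes the trial. On the assumptions above, a team-level test at 151 per arm has about 46% power at ICC 0.01 and 22% at ICC 0.05. Leaving team out does not recover that power; it only hides the loss.

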#### Secondary outcome measures

The following secondary outcome measures will be used to gain more insight into the effects of the Victoria intervention.*Acknowledgement of adversities* related to societal participation is assessed through a self-report questionnaire developed for this study.*Knowledge on rehabilitation and adversities* will be measured through questions for MHP on the domains and phases of the BPR, and through questions on recent conversations about adversities. These questions are also developed for this study.*Self-efficacy* in mental health-related beliefs is measured through the Mental Health Confidence Scale (MHCS) [48], with a 6-point Likert scale, ranging from ‘totally no confidence’ to ‘full confidence’. Cronbach’s alpha for the total scale is 0.93 [49].To measure the *quality of life* the Manchester Short Assessment of Quality of Life (MANSA) is used [50, 51]. The MANSA has good internal consistency (α = 0.72) and is highly correlated (*r* = > 0.83 for each domain) with the Lancashire Quality of Life Profile (LQLP) [50]. The scale consists of 12 questions with a 7-point Likert scale ranging from ‘couldn’t be worse’ to couldn’t be better’ and 4 questions that are answered with yes/no.*General psycho-social functioning* is measured through the Health of the Nation Outcome Scale (HoNOS), a scale that is standard in MHC in the UK [52]. The MHP scores each item on a scale from 0 to 4. The intra class correlation coefficient is 0.92, Cronbach’s alpha is 0.78 and it correlates well with other scales [53]. Moreover, the HoNOS is sensitive to measure change in people with SMI.

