#### Additional and control measures

The following measures include instruments that are possible confounding, mediating or control variables.*Socio-demographic characteristics* will be gathered at the start of the interview, including: age, gender, date of birth, number of children, marital status, nationality, education, living situation, income, and number of years in MHC.*Current diagnosis* is gathered from the questionnaire for the MHP.*Social Support* will be derived from the Inventory of Social Reliance (ISR) [54]. It consists of 11 items on emotional and practical support on a 4-point scale ranging from ‘almost never’ to ‘almost always’. The ISR is a frequently used questionnaire for people with SMI and has good psychometric properties [55].*Neighborhood nuisance* is measured through Sections 1 and 2 of the Safety Monitor (see primary outcome measures for more information). These sections contain 9 questions about the experienced safety and contentment in and about their neighborhood.*Perpetration* is assessed with the Safety Monitor. For the same criminal victimization incidents the participants are asked whether they were a perpetrator ever in their life, and if yes, also in the last year.*FACT fidelity* is assessed through the fidelity scores from the CCAF, the Dutch organization that certifies F-ACT teams. The fidelity score is a mean score on 60 items that ranges from 0 to 5, where 0 means ‘no certificate’ and 5 means ‘optimal implementation’.*Adherence to rehabilitation principles* is measured through a sample of the treatment plans of the clients that participate. This treatment plan consists of agreements, goals and wishes on several life domains for the following year.

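### The client-only random-effects model is extended to two secondary outcomes supplied by professionals (HoNOS and the knowledge questionnaire), whose structure it does not fit

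*Protocol article*

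**What the plan says.** The Statistical analyses section sets out one model for the main outcomes. Its random effects are "Measurements over time are nested within participants; therefore, random slopes will be added for time" and "Random intercepts will be added for the participants". The Design section says who the participants are: "Participants include adult clients of eight F-ACT teams". The cluster design is given as a reason for using a generalized linear mixed model, but no random effect for team or professional is named. On the comparison itself, the section says that "both conditions will be compared after 9 and 18 months follow-up with time as a categorical variable". It then extends the model: "The same procedure will be adopted for secondary outcome measures".

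Table 1 lists five secondary outcomes. Three are at client level. Two are at professional (MHP) level: general psycho-social functioning (HoNOS) and knowledge on rehabilitation and adversities. The Secondary outcome measures section confirms that the professional scores the HoNOS items. The knowledge outcome "will be measured through questions for MHP on the domains and phases of the BPR", and also through questions about recent conversations on adversities. Under Additional and control measures, each client's current diagnosis "is gathered from the questionnaire for the MHP". The protocol does not say whether the knowledge questions are on that same form, or whether they are answered once per client or once per professional.

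**The concern.** The protocol names its random effects and then carries them over to outcomes with a different structure. This is a stated rule that does not fit, not a detail left to an analysis plan.

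HoNOS scores given by one professional share that person's scoring habits. Teams are randomized, so professionals lie mostly within one arm, and the shared component adds to the variance of the arm difference. A model with client effects only does not count it, so standard errors for a follow-up comparison come out too small.

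For the knowledge outcome the information comes from the professional, and the client is at best an indirect unit.

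Two secondary research questions are touched. HoNOS serves the first, as psychosocial functioning. The knowledge questionnaire serves the second, on awareness and acknowledgement by professionals.

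**Working it through.** **The plan's own figures.** The protocol gives no figure for the professional-level outcomes. Its sample size of 151 per condition reproduces with two measurements and a standard deviation of 1: (1.960 + 0.842)² × 2 × (1 + 0.20) / (0.25² × 2) = 150.7. That figure does not bear on this point. The recruitment target does: 2 × 173 = 346 clients over eight teams is about 43 per team, from a caseload of at least 1500 / 8 = 187.5 per team. One professional will therefore normally rate several study clients.

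**HoNOS, follow-up comparison.** Let m be the study clients per professional and ICC the correlation between scores from the same professional. Both are assumptions, because the protocol gives neither.

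- Design effect: DE = 1 + (m − 1) × ICC
- True two-sided error of a nominal 5% test: 2 × [1 − Φ(1.96 / √DE)]

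| m | ICC 0.05 | ICC 0.10 | ICC 0.20 |
|---|---|---|---|
| 4 | DE 1.15, 0.068 | DE 1.30, 0.086 | DE 1.60, 0.121 |
| 5 | DE 1.20, 0.074 | DE 1.40, 0.098 | DE 1.80, 0.144 |
| 8 | DE 1.35, 0.092 | DE 1.70, 0.133 | DE 2.40, 0.206 |
| 12 | DE 1.55, 0.115 | DE 2.10, 0.176 | DE 3.20, 0.273 |

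**Check by simulation.** 4000 runs per setting used eight teams of 44 or 45 clients, no true effect and no extra team variance. A t-test on client records stood in for the client-only model.

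- Follow-up comparison on client records: size 0.07 to 0.13 with m = 4, and 0.10 to 0.23 with m = 9, for ICC 0.05 to 0.20. This agrees with the formula.
- Change from baseline, rater effect constant over time: 0.046 to 0.058. The constant effect cancels within the client.
- Change from baseline, half of the rater variance specific to the time point: 0.07 to 0.31 (m from 4 to 11).
- Team means compared with 6 degrees of freedom: 0.044 to 0.058 throughout.

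**Knowledge questionnaire.** There are two readings, and the protocol does not choose between them.

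- Completed once per client: the items on the domains and phases of the rehabilitation approach ask what the professional knows, so one person's answers are repeated over that person's clients. Items on recent conversations can still differ by client.
- Completed once per professional: nothing is repeated, but the record does not belong to a client. A client random intercept is then the wrong unit, and the repeated measurements are nested in professionals instead.

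The model cannot be applied unchanged on either reading.

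**The case against.** The strongest objection concerns the contrast. HoNOS is also measured at baseline and time is categorical. If the test is arm-by-time, a stable rater effect is absorbed by the client intercept and the size stays near 5%. This stands, but it is conditional. The wording describes a comparison of conditions at 9 and 18 months and does not fix an arm-by-time test. The Discussion also expects staff to move between teams, so raters may change.

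A second objection is that the rater component may be small: the protocol reports an intraclass coefficient of 0.92 for HoNOS. Its type is not stated. If it is inter-rater, and 0.08 is taken as the rater share, m = 5 gives DE 1.32 and an error of 0.09, and m = 8 gives DE 1.56 and 0.12. This supports the lower part of the range but does not remove the inflation.

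Third, the missing team term affects every outcome, and adding one with small-sample degrees of freedom would largely restore the size of the HoNOS comparison. That is right. It would not settle the unit of the knowledge outcome.

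Fourth, the Randomization and blinding section promises to correct for staff changes and for clients switching teams. That concerns movement, not several clients sharing a rater.

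A reader might infer a stronger claim: that knowledge records are certainly duplicated, with a correlation near 1 and an error of 38% at five clients per professional (DE 5.0). The protocol does not support this. Completion per client is only suggested by the source of the diagnosis. Even then, only the rehabilitation-knowledge items would repeat, not the whole measure. Nor is there support for a correlation of 0.3 or more for HoNOS, which at five clients would mean an error of 19% or higher.

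**Conclusion.** The point holds in a limited form. The instruction to reuse the client-level model does not fit the two professional-level outcomes.

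For HoNOS, the follow-up comparison as worded is too liberal. The true error is about 7% to 27% against a nominal 5%, and about 7% to 14% with five clients per professional. This rests on assumed values of 4 to 12 clients per professional and an ICC of 0.05 to 0.20, and on professionals lying mostly within one arm. Under an arm-by-time test with constant rater effects there would be little or no inflation.

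For knowledge, the fault is an undefined unit, and no single error rate can be attached to it. Both are secondary outcomes, and the primary conclusions do not depend on this point.

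**What to change.** Exempt HoNOS and the knowledge questionnaire from the sentence that extends the main model, and record a professional identifier with every record that a professional supplies. Then state the following:

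- **Knowledge:** whether the form is completed per professional or per client. Analyse it with the professional as the unit, using one record per professional per time point for items that do not vary by client, with professional and team effects.
- **HoNOS:** effects for client, rating professional and team, with the professional crossed with team where staff serve several teams. State also whether the test is the difference at follow-up or arm-by-time.
- **Both:** small-sample degrees of freedom suited to eight teams. Random intercepts alone, tested against a normal reference, would not secure the error rate.

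The cost is a few sentences of analysis wording and one identifier field on an existing form. Intervals for these two outcomes will be wider.
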